### Blood testing protocol in translational research

The blood samples are collected T1 and T4. After overnight fasting for 10 h, blood samples (10 mL) are collected in the morning before the start of anti-cancer treatment (T1) and at the end of the NEXTAC protocol (T4). The blood collection tubes contain ethylenediaminetetraacetic acid disodium salt as an anticoagulant and are immediately placed in ice water or an ice-cold cooling container for longer than 15 min. Plasma is separated by centrifugation at 1500 g and 4 °C for 15 min. One-tenth of the volume of 1 N HCL is added to the separated plasma for ghrelin analysis. Samples are stored at − 80 °C until analysis. After thawing, the plasma samples are deproteinized using acetonitrile at a final concentration of 80% before the measurement of amino acid concentrations by high-performance liquid chromatography–electrospray ionization–mass spectrometry by precolumn derivatization [24]. Plasma levels of acyl ghrelin and des-acyl ghrelin are measured using enzyme-linked immunosorbent assay kits according to the manufacturer’s instructions.

## Discussion

The NEXTAC-TWO study is a multicenter, randomized phase II study evaluating the efficacy of nutritional and exercise interventions in patients with chemo-naïve advanced NSCLC or pancreatic cancer. After the baseline assessment, the participants are randomized to either the intervention group, which receives the multimodal intervention (NEXTAC program), or to the control group, which receives standard care alone.

The primary endpoint of this study is disability-free survival. We originally defined this endpoint to detect the effectiveness of the multimodal intervention with regard to enabling the patient to maintain their activity level during cancer therapy. A similar endpoint was used as the primary endpoint in a large phase III trial that investigated the efficacy of aspirin in the elderly population [25]. It is important not only to prolong survival but also to maintain elderly patients’ ability to perform daily life activities during cancer treatment. The evidence validating the use of these types of endpoints is insufficient. We will perform this trial and try to suggest a new endpoint for future supportive care trials for cancer patients. Furthermore, this trial also plans to evaluate improvements in nutritional status, physical condition, QOL, ADL, survival and safety as secondary endpoints.

Recently, anti-cachectic agents have been developed. Anamorelin, a novel ghrelin-receptor agonist, resulted in increased LBM in the ROMANA1/RONAMA2 trial [26]. However, this agent did not result a significant benefit with regard to the handgrip strength test. Those results were reproduced in the Japanese phase II trial [27]. These results suggest that additional interventions involving anti-cachectic agents will improve motor function and maintain ADL in cachexic patients. The combination of these emerging anti-cachectic agents and nonpharmacological interventions will be the next step to improve the ADL and QOL of cachexic patients. Our NEXTAC program is a promising candidate to use in combination with anti-cachectic agents.

To the best of our knowledge, this is the first randomized trial to evaluate the efficacy and safety of a multimodal intervention for elderly cancer patients involving interprofessional collaboration.

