9) History of acute myocardial infarction, unstable angina, uncontrollable hypertension, and symptomatic sustained arrhythmia within 6 months. Stable atrial fibrillation treated with appropriate anticoagulation therapy is allowed.	
10) Uncontrollable diabetes mellitus	
11) Patients whose appropriate period has not passed since prior treatment	
i. Surgery: 7 days	
ii. Palliative radiation: 1 day	
iii. Minor surgery (i.e. biopsy): 1 day	
12) Screening failure	
i. Patients who failed to wear the accelerometer for more than 4 days	
ii. Patients who could not properly handle the accelerometer	
iii. Patients who failed to initiate first-line therapy within 14 days of enrollment	

This study consisted of two periods, namely, the screening period and the study period (Fig. 1). In the screening period, after written informed consent is obtained, the investigator educates the eligible patients regarding the wearing and handling of an accelerometer. Patients who demonstrated their ability to wear and handle the accelerometer for at least 4 days are enrolled and randomized. If the patients cannot wear the accelerometer or the investigator determines that the patient is not able to handle the accelerometer adequately, the patient is judged to be ineligible and is not enrolled in the study. The study period is defined as the time between the date of study enrollment and the date of the occurring disability event or death.

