### Assessments and interventions

The details of the assessment and exercise program in the NEXTAC-TWO study are shown in Table 2. There are no restrictions in concomitant care or interventions in both intervention and control group. No provision for ancillary or post-trial care is planned.

**Table 2 Tab2:** Assessments and interventions

			Control arm			Intervention arm		
Sessions		Time point^a^	T1	T2/T3	T4	T1	T2/T3	T4
		Detail of assessment/intervention						
Nutritional sessions 30 min at T1 20 min at T2, T3, and T4	Assessments	•Food intake	○	–	○	○	○	○
		• Nutritional status (MNA^d^)	○	–	○	○	○	○
		• Nutritional checklist^b^	○	–	○	○	○	○
		•Skeletal muscle analysis	○	–	○	○	–	○
		•Diet diary collection	–	–	–	–	○	○
	Interventions	• Nutritional advice	–	–	–	○	○	○
		• Support for NIS^d^ management, food environment, and eating-related distress	–	–	–	○	○	○
		• ONS^d^ prescription^c^	–	–	–	○	○	–
Exercise session 30 min at T1 20 min at T2, T3, and T4 each for A and B.	Assessments	• Assessment of physical function (Hand-grip strength, SPPB^d^)	○	–	○	○	–	○
		• Exercise diary collection	–	–	–	–	○	○
		• Assessment of physical activity (Physical activity measurement, Physical activity interview)	○	–	–	○	○	○
		• EORTC-QLQ-C30 questionnaire	○	–	○	○	–	○
	Interventions	A. Home-based resistance training						
		• Prescription (T1) and modification (T2, T3, T4) of exercise program	–	–	–	○	○	○
		• Instruction of exercise procedures	–	–	–	○	○	○
		•Education of self-modification	–	–	–	○	○	○
		B. Physical activity promotive counseling						
		• Prescription of target daily step	–	–	–	○	○	○
		• Physical activity counseling	–	–	–	○	○	○
		• Education of fall prevention	–	–	–	○	○	○

^a^Baseline assessments were performed during the time between study entry and initiation of chemotherapy (T1 point). Subsequent assessments were at 4 ± 2 (T2 point), 8 ± 2 (T3 point), 12 ± 2 (T4 point) weeks after the study enrollment

^b^Nutritional checklist to collects information about presence or absence of nutrition impact symptoms, problems in food environment, or eating-related distress

^c^A branched-chain amino-acids rich oral nutritional supplement (Inner Power®, Otsuka Pharmaceutical Co., Ltd., Japan) was provided one pack daily for 12 weeks

^d^*MNA* Mini-nutritional assessment, *NIS* nutrition impact symptoms, *ONS* oral nutritional supplement, *SPPB* Short Physical Performance Battery

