#### Time points of assessments and interventions

Exercise and nutritional assessment data are collected at four time points during the study period; baseline assessments are performed during the study entry until the administration of the first systemic therapeutic measure (T1 point). Systematic therapy includes cytotoxic chemotherapy, immunotherapy using an immune checkpoint inhibitor or targeted therapy using a tyrosine kinase inhibitor. These factors include stratification factors (cytotoxic chemotherapy or immunotherapy/targeted therapy). Subsequent assessment points occur at 4 ± 2 (T2 point), 8 ± 2 (T3 point) and 12 ± 2 (T4 point) weeks after randomization. After the T4 point, follow-up assessments including the determination of the modified Katz index score are performed at 8 ± 4-week intervals. In the control group, exercise and nutritional assessments are performed at the T1 and T4 assessment points. In this group, interventions are not performed at any assessment point. In the intervention group, exercise and nutritional interventions are performed at the T1-T4 points.

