#### Physical and exercise assessment

The physiotherapists assess the handgrip strength and short physical performance battery (SPPB) score according to the study protocol. The medical doctor, physiotherapist or nurse administers the lifestyle questionnaire in an interview and educates the participant about lifestyle measures needed to ensure their safety and to maintain the prescribed amount of physical activity. The lifestyle questionnaire includes information about the family structure, occupational status, the amount of physical activity on a usual day, routine habits and housework, participation in sports or exercise, frequency of going out, and experiences of falls. Physical activity is measured using an accelerometer (Lifecorder®, Suzuken Co. LTD., Nagoya, Japan) at the protocol-defined assessment intervals. The QOL assessments are performed at T1 and T4 using the EORTC-QLQ-C30 questionnaire.

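### The article contradicts itself on whether T1 baseline measurements come before or after randomization, so effort-dependent and self-reported baselines may be taken once the arm is known

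*Protocol article*

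**What the plan says.** The protocol article places baseline relative to randomization in several places.

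- **Discussion:** "After the baseline assessment, the participants are randomized to either the intervention group". Baseline comes first, then allocation.
- **Study design and participants:** "Patients who demonstrated their ability to wear and handle the accelerometer for at least 4 days are enrolled and randomized". Enrollment and randomization are one step after screening. The same section adds: "The study period is defined as the time between the date of study enrollment and the date of the occurring disability event or death".
- **Time points of assessments and interventions:** "Exercise and nutritional assessment data are collected at four time points during the study period". T1 is the first of the four. Its window is given as "baseline assessments are performed during the study entry until the administration of the first systemic therapeutic measure (T1 point".
- **Table 2, footnote a:** the same window in other words, "Baseline assessments were performed during the time between study entry and initiation of chemotherapy (T1 point".
- **Time points of assessments and interventions**, on delivery: "In the intervention group, exercise and nutritional interventions are performed at the T1-T4 points". Table 2 agrees, with nutritional advice, exercise prescription and activity counseling all ticked at T1 in that arm only.
- **Physical and exercise assessment:** "The physiotherapists assess the handgrip strength and short physical performance battery (SPPB) score according to the study protocol". The section on exercise and lifestyle interventions has a physiotherapist teach the training program at T1.

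**The concern.** The order of baseline and allocation decides whether a T1 value is a true pre-randomization measurement. Grip strength and SPPB depend on effort. QLQ-C30, the 24-hour recall and much of the MNA depend on what the patient reports. The control arm visibly receives no intervention, and the article describes no blinding of assessors. If T1 follows allocation, a patient's effort or answers, or the assessor's encouragement, can differ by arm at baseline itself. That difference then enters any comparison of change from T1 as if it were a treatment effect of opposite sign. In the control arm these measures are scheduled only at T1 and T4, so any change comparison rests on a single baseline value.

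At stake are secondary endpoints 2 to 4 in Table 3 (physical function, nutritional status, quality of life), to the extent that they use these measures. Both the Abstract and the Discussion speak of evaluating improvements in these domains, which makes a change-from-baseline reading natural.

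**Working it through.** The plan gives no figure on this point to reproduce. The check is a comparison of texts, followed by short algebra on the consequence.

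**Step 1. When does T1 fall?**

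| Source in the article | Statement | Implied order |
|---|---|---|
| Discussion | Randomization follows the baseline assessment | T1, then randomization |
| Study design and participants | Enrolled and randomized together after screening; study period opens at enrollment | Randomization at the start of the study period |
| Time points section | All four time points lie in the study period | T1 not before enrollment |
| Time points section; Table 2 footnote a | T1 runs from study entry to first systemic therapy | T1 at or after entry |
| Time points section; Table 2 | Intervention delivered at T1 in one arm | Allocation known by the end of the T1 session |

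**Step 2. Is enrollment the same date as randomization?** The footnote to Table 2 times T2 to T4 from enrollment. The time points section times the same visits, with the same 4, 8 and 12 week targets, from randomization. With the one-step wording in the design section, the article treats the two dates as one. The Methods therefore put T1 at or after randomization, and the Discussion puts it before.

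**Step 3. Could the Discussion mean something other than T1?** The only assessment that the Methods clearly place before randomization, apart from eligibility checks, is the accelerometer screen. The article uses the term baseline assessments elsewhere only for T1, so that reading is strained.

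**Step 4. Consequence if T1 follows allocation.** Let d be the between-arm difference in mean T1 caused by knowing the arm, with T4 unaffected by it.

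- Change score (T4 - T1): the bias in the arm difference is 0 - d = -d.
- ANCOVA on T4 with T1 as covariate: the bias is about -rho × d, where rho is the T1-T4 correlation and the variances are similar. The documents give no rho. For an assumed 0.5 to 0.7, the bias is -0.5d to -0.7d.
- T4 values compared directly: T1 is not used, so the bias from this source is 0.

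The article supplies neither d nor its sign, so none of these becomes a number in grip-strength or questionnaire units.

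**Step 5. How late could T1 be?** The only bound is the exclusion rule that first-line therapy must start within 14 days of enrollment. If enrollment there means randomization, T1 could fall up to 14 days afterwards. That is an outer limit on starting therapy, not a T1 schedule.

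**Step 6. Which endpoints are exposed?** Disability-free survival and overall survival run from random assignment and use no T1 value. CT muscle mass does not depend on effort. Sample size and power are unaffected.

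**The case against.** The strongest reply is that measurement after allocation is inferred and nowhere stated. The T1 window is worded from study entry, not from randomization, and nothing says when the arm is disclosed. A sequence of assessments, then allocation, then the first intervention session would satisfy the Discussion and still deliver the intervention at T1. The study schema and the full protocol are not shown and might settle it. This stands as a limit: the finding is a contradiction that leaves the risk open, not proof that baselines were taken unblinded. It does not remove the contradiction, because the Methods and the Discussion state opposite orders.

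Four stronger readings are tempting and are not supported.

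- A reader might infer that T1 is routinely two weeks after randomization. The 14-day rule is listed under screening failure, where enrollment may be used loosely, and it is only a ceiling.
- A reader might infer that every functional, nutritional and quality-of-life comparison depends on T1. The statistical section names only the Wilcoxon rank-sum test for continuous measures. It mentions no change score, ANCOVA or baseline covariate, and a comparison of T4 values would not use T1. For physical activity, accelerometer wear of at least 4 days precedes randomization in any case.
- A reader might infer that patients who worsen before T1 are lost without a baseline. Nothing in the article indicates such losses.
- A reader might infer that the Katz assessment has the same problem. Katz status is an exclusion criterion and must already be known before entry.

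**Conclusion.** The concern holds as a contradiction in the current text with a limited consequence. Read as written, the Methods allow effort-dependent and self-reported baselines to be taken after the arm is known, while the Discussion says that they are taken before. Any change-from-T1 comparison of grip strength, SPPB, MNA, recalled intake or QLQ-C30 could then be biased by -d, with d unknown in size and direction.

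This rests on three assumptions: that enrollment and randomization are the same date, as the article's interchangeable use suggests; that the arm is not withheld until the measurements are done; and that change from T1, or adjustment for it, is analyzed. If any of them fails, the bias does not arise, though the wording would still need correcting. The primary endpoint, overall survival and CT muscle mass are essentially untouched. The point is worth acting on because the protection is cheap and recruitment was still open when the article was written, but it does not threaten the trial's main conclusion.

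**What to change.** Reconcile the design section, Table 2 footnote a, the time points section and the Discussion so that all give one order. T1 measurements (grip strength, SPPB, MNA, 24-hour recall, QLQ-C30) should be completed before randomization. If the logistics do not allow that, they should be completed at least before the allocation is disclosed to patient and assessor. The first intervention session follows. If sites already work this way, correcting the Methods wording is enough.

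For patients already enrolled, record whether T1 preceded allocation. Where it did not, also report the between-arm comparison of T4 values without T1 adjustment as a sensitivity analysis. An analysis restricted to pre-allocation baselines should not be relied on instead, since it could have few or no patients if sites followed the Methods wording.

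Costs: some baseline assessments on patients who then fail screening, and possibly a T1 session split in two for nutritionists and physiotherapists at 15 institutions. Disclosing the arm only after the measurements, within the same visit, would avoid the split. A change made during recruitment also leaves two baseline timings in one trial, which is a further reason to record the order for every patient. The T4-only analysis gives up whatever precision a valid baseline would have added.

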### Status of the trial

The NEXTAC-TWO study started in August 2017 and patient recruitment is ongoing at February 26, 2019.

## Data Availability

The datasets used and/or analyzed during the current study are available from the corresponding author on reasonable request.

## Abbreviations

CT: Computed tomography
EORTC-QLQ-C30: The European Organization for Research and Treatment of Cancer Quality of Life Questionnaire
MNA score: Mini Nutritional Assessment score
SPPB score: Short Physical Performance Battery score
